## Abstract

**Background:**

Trifluridine/tipiracil (FTD/TPI) prolongs survival in the third- or later-line treatment for advanced gastric cancer (GC), esophagogastric junction (EGJ) adenocarcinoma, and colorectal cancer. While single-arm phase II trials showed promising outcomes of FTD/TPI plus ramucirumab (RAM) as third- or later-line treatments for advanced GC or EGJ cancer, there have been no clinical trials to directly compare FTD/TPI plus RAM with FTD/TPI monotherapy. Therefore, we have started a randomised phase II trial to evaluate the efficacy and safety of FTD/TPI plus RAM compared with FTD/TPI monotherapy as third- or later-line treatments in patients with advanced GC and EGJ adenocarcinoma.

**Methods:**

This RETREVE trial (WJOG15822G) is a prospective, open-label, randomised, multicentre phase II trial comparing FTD/TPI plus RAM versus FTD/TPI monotherapy in a third- or later-line setting. Eligibility criteria include age of > 20 years; performance status of 0 or 1; unresectable or recurrent gastric or EGJ adenocarcinoma; confirmed HER2 status; refractory or intolerant to fluoropyrimidine, taxane or irinotecan; refractory to RAM (not intolerant); and at least a measurable lesion per RECIST 1.1. FTD/TPI (35 mg/m^2^ twice daily, evening of day 1 to morning of day 6 and evening of day 8 to morning of day 13) was administered orally every 4 weeks, and RAM (8 mg/kg) was administered intravenously every 2 weeks. The primary endpoint is progression-free survival (PFS), and the secondary endpoints are overall survival, objective response rate, disease control rate, and safety. The expected hazard ratio of PFS is set as 0.7, assuming 4-month PFS rate of 27% in FTD/TPI monotherapy and 40% in FTD/TPI plus RAM. The number of subjects was 110, with a one-sided alpha error of 0.10 and power of 0.70.

**Discussion:**

This study will clarify the additional effect of RAM continuation beyond disease progression on FTD/TPI in the third- or later-line setting for patients with advanced GC or EGJ cancer.

**Trial registration:**

jRCTs041220120.

**Supplementary Information:**

The online version contains supplementary material available at 10.1186/s12885-023-11199-1.

## Background

Gastric cancer (GC) is the fifth most common and fourth most deadly cancer worldwide [1]. It is more common in East Asia than in the Western countries. It is difficult to cure in patients with recurrent or unresectable GC or esophagogastric junction (EGJ) cancer, and systemic chemotherapy is recommended to prolong survival and control disease related symptoms. Despite recent developments in chemotherapy, the prognoses remain poor.

As later-line treatment in patients with advanced gastric and EGJ adenocarcinoma, monotherapy with trifluridine/tipiracil (FTD/TPI), irinotecan, and nivolumab are recommended in the Japanese treatment guideline, regardless of HER2 status [2–7].

FTD/TPI is an oral cytotoxic chemotherapeutic agent comprising trifluridine, an antineoplastic thymidine analog, and tipiracil, which prevents trifluridine degradation. The TAGS, an international joint phase III study to examine the prolongation of overall survival (OS) of FTD/TPI over placebo in patients with unresectable or recurrent gastric cancer refractory to standard treatment, showed that FTD/TPI monotherapy was significantly superior to the placebo (hazard ratio [HR]: 0.69, 95% confidential interval [CI]: 0.56–0.85, one-sided *p* = 0.00029) [2]. In that study, disease control rate (DCR) and median progression-free survival (PFS) in the FTD/TPI arm were not satisfactory, 44% and 2.0 months, respectively. Thus, survival benefits of anti-cancer drugs in the later-line treatment of patients with gastric and EGJ adenocarcinomas are limited, and further development of later-line chemotherapy is warranted.

Recently, combination therapy with FTD/TPI and angiogenesis inhibitors for pre-treated patients with gastric or EGJ adenocarcinoma has been implemented globally. In Japan, a single-arm phase II study of FTD/TPI plus ramucirumab (RAM) showed promising outcomes in terms of tumour response, PFS, associated with the feasible safety profile [8]; 31 patients refractory to RAM showed an objective response rate (ORR) and DCR of 16% and 77%, respectively, and the median PFS of 5.3 months in third- or later-line treatment. These outcomes of FTD/TPI plus RAM seemed better than those of the FTD/TPI arm in the TAGS trial. However, it remains unclear whether FTD/TPI plus RAM is superior to FTD/TPI monotherapy. Therefore, we planned a randomised phase II trial to evaluate the efficacy and safety of FTD/TPI plus RAM compared with FTD/TPI monotherapy as third- or later-line treatments in patients with advanced GC or EGJ cancer refractory to RAM.

## Methods/design

### Objectives

The objective of this RETRIEVE study (WJOG15822G) is to evaluate the efficacy and safety of FTD/TPI plus RAM as a third- or later-line treatment for patients with unresectable or recurrent GC or EGJ cancer, compared with FTD/TPI monotherapy. The primary endpoint is PFS and the secondary endpoints are OS, ORR, DCR, and safety.

### Study design

This is a prospective, open-label, randomised, multicentre phase II study, conducted in 47 centres of the West Japan Oncology Group (WJOG) in Japan (Fig. 1). The patients were randomised in a 1:1 ratio to FTD/TPI monotherapy (Arm A) or FTD/TPI plus RAM (Arm B). Randomisation is performed centrally with the minimisation method, with stratification for ECOG Performance Status (PS, 0 vs 1), prior use of nivolumab (no prior use vs immediate prior treatment line vs other treatment line), and prior use of RAM (immediate prior treatment line vs other treatment line). Key inclusion criteria include: 1) age of 20 years or over, 2) ECOG PS 0 or 1, 3) histological diagnosis of primary gastric or EGJ adenocarcinoma, 4) unresectable or recurrent disease confirmed by computed tomography (CT), 5) failure (refractory or intolerant) of prior chemotherapy with fluoropyrimidine and taxanes or irinotecan (patients are eligible even if they have used both drugs), refractory to RAM containing chemotherapy, 6) one or more measurable lesions per RECIST (Table 1). Key exclusion criteria include: 1) synchronous active malignancy, 2) prior use of FTD/TPI, 3) massive ascites or palliative ascites drainage within 2 weeks, 4) brain metastasis and tumour invasion to the central nervous system, 5) active bleeding and uncontrolled hypertension, heart disease, and diabetes mellitus, 6) intestinal obstruction, gastrointestinal perforation, and inflammatory bowel disease, 7) arterial thrombosis or venous thrombosis such as deep vein thrombosis and pulmonary embolism, 8) active infection,.

**Fig. 1 Fig1:**
[figure not shown]
Study schema of RETRIEVE study

**Table 1 Tab1:** Key eligibility criteria for the RETRIEVE study

**Inclusion criteria**	**Exclusion criteria**
1) Age of 20 years or above 2) ECOG PS of 0 or 1 3) Histologically diagnosed as gastric adenocarcinoma or EGJ 4) Unresectable progression or recurrence confirmed by CT scan 5) Prior use of fluoropyrimidine, taxanes or irinotecan (patients are eligible even if they have used both drugs), ramucirumab (eligible only for refractory cases) 6) One or more measurable lesions by RECIST version 1.1 7) HER2 test has been performed before registration 8)) Expected to survive for 3 months or more 9) Adequate organ and bone marrow function 10) Written consent has been obtained	1) Active double cancer (simultaneous double cancer / multiple cancer and metachronous double cancer or multiple cancer with a disease-free period of 2 years or less) 2) Difficulty with oral intake. Specifically, cases that require daily infusion for purposes of nutrition and water intake 3) Pre-treatment including FTD/TPI in the past 4) Hypersensitivity to the drugs used in this study 5) Past history of major surgery (general anaesthesia required) within 4 weeks and/or radiation therapy covering the abdomen within 2 weeks before registration 6) Cases with severe pleural effusion 7) Cases with severe ascites or a history of palliative ascites puncture within 2 weeks before registration 8) Cases with brain metastasis and tumor metastasis to the central nervous system 9) Adverse events (non-haematological toxicity) of poorly controlled Grade 2 or higher (CTCAE v5.0) remain at the time of registration (patients with hair loss, dysgeusia, pigmentation, or peripheral neuropathy may still be registered even if Grade 2 or higher) 10) Local or systemic active infection that requires treatment 11) Uncontrolled hypertension or diabetes mellitus despite adequate treatment 12) Unstable angina within 4 weeks prior to enrolment, uncontrolled heart failure, arrhythmia requiring treatment; excluding arrhythmias that are not clinically problematic 14) Serious haemorrhagic disorders or vasculitis. Cases with significant gastrointestinal bleeding episodes (Grade 3 or higher) within 12 weeks prior to enrolment 15) Past history of gastrointestinal perforation or fistula within 24 weeks prior to registration. Past history of gastrointestinal obstruction or inflammatory bowel disease such as Crohn's disease. However, regarding gastrointestinal obstruction, cases in which colostomy or bypass surgery has been performed in the past and oral intake is sufficiently possible are included 16) Past history of unrecovered trauma, active gastric ulcer, or fracture within 4 weeks prior to enrolment 17) Past history of arterial thrombosis (including myocardial infarction and cerebral infarction) within 24 weeks before registration 18) History of deep vein thrombosis or pulmonary artery thrombosis (excluding catheter thrombosis and superficial thrombosis) within 12 weeks before registration. However, anticoagulation for the prevention of thrombosis is allowed if coagulation function has been stable for at least 12 weeks prior to enrolment (PT-INR ≤ institutional maximum × 1.5) 19) Immune deficiency (such as HIV infection), autoimmune diseases with administration of systemic steroids 20) Patients taking antiplatelet drugs. Low doses of aspirin (less than 325 mg/day) and non-steroidal anti-inflammatory drugs (NSAIDs) are permitted 21) Continuous use of systemic steroids (excluding contrast agent allergy prophylaxis, pre-medication of anti-cancer agents, hydrocortisone replacement therapy for adrenal hypofunction of immune-related adverse events) and immunosuppressive agents 23) HBs-Ag is positive. However, patients can still be registered if HBV infection is controlled by a nucleic acid analogue preparation and no presence of HBV-DNA is confirmed 24) Pregnant women, lactating women, women who may be pregnant or who are not willing to use contraception 25) Difficulty enrolling in this study due to a clinical problem involving mental illness

### Procedures

FTD/TPI (35 mg/m^2^) was administered orally, twice daily for 10 days from the evening of day 1 to the morning of day 6, and from the evening of day 8 to the morning of day 13, repeated in a 4-week cycle in both arms. RAM (8 mg/kg) is administered intravenously on days 1 and 15 in each cycle of the arm B. RAM is administered for 60 min first, and a second and sequential dose of RAM can be administered for 30 min if tolerability of RAM is confirmed. The protocol treatment is continued until disease progression, unacceptable toxicities, or withdrawal of consent.

Three dose reduction levels were set: 35 (starting level), 30 (level -1), 25 (level -2), and 20 mg/m^2^ (level -3) for FTD/TPI, and two dose reduction levels are set: 8 mg/kg (level 0), 6 (level -1), and 5 mg/kg (level -2) for RAM. In both treatment groups, if Grade 4 neutropenia or thrombocytopenia, Grade 3 or worse febrile neutropenia, or Grade 3 non-hematologic adverse events associated with FTD/TPI is observed, the dose of FTD/TPI is reduced to the next lower dose. If life-threatening FTD-/TPI-related adverse events occur, FTD/TPI is discontinued. If patients experience proteinuria showing 3 + on a urine dipstick or 2–3 g/24 h, or if Grade 3 RAM-related adverse events, except hypertension and proteinuria, are observed, the dose of RAM is reduced to the next lower dose. If patients experience Grade 3 infusion reaction, 4 + on a urine dipstick or ≥ 3 g/24 h proteinuria, or uncontrolled hypertension, RAM is discontinued.

### Assessment

Tumour was assessed using CT scan of the chest, abdomen, and pelvis within 2 weeks before randomisation and every 8 weeks after randomisation until discontinuation of the protocol treatment. Patients are required to visit the hospital every 2 weeks to check their physical condition and adverse events during the protocol treatment. Laboratory tests are performed within 2 weeks before randomisation and repeated every 2 weeks after randomisation until discontinuation of the protocol treatment.

### Evaluation of outcomes

PFS is defined as the time from randomisation to disease progression or death from any cause. OS is defined as the time from randomisation to death from any cause. Tumour response is assessed according to the RECIST (version 1.1). Objective response rate (ORR) is defined as the proportion of patients with a complete response or partial response to treatment. DCR is defined as the proportion of patients with a complete response, partial response, or stable disease. The severity of each adverse event is graded according to the National Cancer Institute Common Terminology Criteria for Adverse Events (version 5.0).

### Sample size calculation and statistical analysis

The statistical hypothesis is set with reference to the PFS of previous clinical studies in advanced GC. The PFS rate at 4 months was reported as approximately 27% in the FTD/TPI arm of the TAGS trial [2]. Considering that the patients enrolled in a previously reported phase II study of FTD/TPI plus RAM were in good general health [8], the expected 4-month PFS rate in the FTD/TPI plus RAM arm of this study is referred to 40% which was the lower limit of the 95% CI of the 4-months PFS rate of FTD/TPI plus RAM in patients with two to four lines of prior chemotherapy (Cohort B) of a previously reported phase II study [8]. Therefore, the expected hazard ratio for PFS is set as 0.7. The minimum sample size for primary analysis is 54 patients per group with an alpha error of 0.1 (one-sided) and power (1-β) of 0.7. The enrolment period is planned to be 1.5 years. Therefore, the sample size of this study is set at 110 subjects to accommodate ineligible patients. The follow-up period for PFS, ORR, DCR, and safety is set to 6 months, and the follow-up period for OS was set to 1 year from the enrolment of the last patient.

The analyses of the primary and secondary efficacy endpoints are planned to be performed in the full analysis set, and additional analysis is planned in the intention-to-treat population and in the per protocol if necessary. The safety analysis is planned to be conducted in the safety analysis population.

Patient characteristics will be compared using Pearson’s *χ*^2^ test for categorical outcomes and Welch’s *t*-test or Wilcoxon’s rank sum test for continuous variables, as appropriate. As a primary efficacy analysis for comparisons between the two groups, a stratified log-rank test using stratification factors will be used, and the HR for PFS and its 80% CI will be calculated using the multivariable Cox proportional hazard model with adjustments for the stratification factors. The secondary analysis of OS will be performed in the same manner as the primary analysis. ORR and DCR will be compared using Fisher’s exact test, and its 95% CI will be estimated. For the safety analysis, the frequencies of worst grade AE and grade 3 and 4 AE will be estimated. All statistical analyses will be fixed prior to database lock.

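### PFS and OS are adjusted only for the three allocation factors; a baseline lesion sum obtainable on every patient could be pre-specified as a covariate, and the baseline significance tests dropped

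*Protocol article*

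**What the plan says.** The statistical section of the protocol article (Sample size calculation and statistical analysis) separates the test from the estimate. The PFS decision comes from a log-rank test stratified by the allocation factors. The HR and its 80% CI are "calculated using the multivariable Cox proportional hazard model with adjustments for the stratification factors". OS follows the same scheme. Under Study design those factors are ECOG PS (2 levels), prior nivolumab (3 levels) and prior RAM (2 levels). No other covariate is named for PFS or OS.

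The only other stated use of baseline data is comparison between arms: "Patient characteristics will be compared using" Pearson's chi-squared, Welch's t or Wilcoxon's rank sum test. The article does not say what a significant result would lead to.

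Entry requires "one or more measurable lesions per RECIST" (Study design), and the Assessment section states: "Tumour was assessed using CT scan of the chest, abdomen, and pelvis within 2 weeks before randomisation". Response is judged by RECIST 1.1, so a baseline sum of target-lesion diameters can be had for every eligible patient.

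The planning figures are "54 patients per group with an alpha error of 0.1 (one-sided) and power (1-β) of 0.7", with 110 to be enrolled, and "the expected hazard ratio for PFS is set as 0.7".

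**The concern.** With planned power of only 0.70 and about 103 PFS events, a source of information that costs no patients deserves use. If baseline tumour burden is prognostic, a model that includes it tests the treatment effect with more power and removes chance imbalance in that factor. The lesion sum is not an allocation factor, so neither the minimisation nor the planned model deals with it.

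Significance tests of baseline characteristics do neither job. After randomisation any significant difference is chance, and for the minimised factors the p-value is pushed towards 1 by design. Such tests recover no precision and are no guide to whether an imbalance matters.

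**Working it through.** **1. The plan's own figure.** Inputs from the article: HR 0.7, one-sided alpha 0.10, power 0.70, 1:1 allocation, 4-month PFS 27% and 40%, 18 months' accrual, 6 months' follow-up (taken as after the last enrolment).

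- HR check: ln 0.40 / ln 0.27 = 0.6998.
- Events (Schoenfeld): 4(1.2816 + 0.5244)² / (ln 0.7)² = 13.05 / 0.1272 = 102.6, so 103.
- Exponential PFS, control hazard −ln(0.27)/4 per month, uniform accrual: mean event probability 0.958.
- Patients: 103 / 0.958 = 107.5, so 54 per group. This agrees with the article.
- Power at 108 patients (103.5 events): 0.703.

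This calculation uses no covariates, so the planned 0.70 does not depend on any.

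**2. What one added covariate brings.** Simulation of 108 patients, 54 per arm at random, 4,000 trials per row (Monte Carlo SE √(0.7 × 0.3 / 4000) = 0.007), with marginal 4-month PFS held at 27% and 40%. Both models contain treatment and the three allocation factors; the second adds one standardised baseline score. Assumed, because the article does not give them: the score's prognostic strength, the factor frequencies, PS log-HR 0.4, and no prognostic effect of prior nivolumab or prior RAM. Minimisation itself was not simulated.

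| Log-HR per SD | HR per SD | Power, allocation factors only | Power, plus score | Gain (points) |
|---|---|---|---|---|
| 0 | 1.00 | 0.700 | 0.698 | 0 |
| 0.2 | 1.22 | 0.700 | 0.722 | 2 |
| 0.3 | 1.35 | 0.695 | 0.721 | 3 |
| 0.4 | 1.49 | 0.691 | 0.748 | 6 |
| 0.5 | 1.65 | 0.662 | 0.754 | 9 |
| 0.7 | 2.01 | 0.665 | 0.824 | 16 |

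Under the null at log-HR 0.4, one-sided rejection was 0.101 without the score and 0.105 with it. A separate simulation put both models at about 0.11, and power at 0.69 in both when the score was not prognostic.

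**3. The same gain in events.** By the formula in step 1, power 0.72 needs 4(1.2816 + 0.583)² / 0.1272 = about 109 events and power 0.75 needs 4(1.2816 + 0.674)² / 0.1272 = about 120, against 103.

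**4. Which analysis gains.** The table concerns the Wald test of treatment in the Cox model. The planned decision comes from the stratified log-rank test, and adding terms to the Cox model leaves that test untouched. In the same simulation a log-rank test over all 2 × 3 × 2 = 12 strata had power of about 0.59 to 0.62. That shortfall is a separate matter of sparse strata. It depends on the assumed frequencies and on any pooling, and is not counted in the gain.

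**5. Baseline tests.** In a simulation of minimisation (3,000 trials of 110 patients, assumed 80% biased coin and assumed frequencies), p < 0.05 occurred in 0 trials for each allocation factor. For 15 other independent characteristics (number assumed), the chance of at least one p < 0.05 is 1 − 0.95¹⁵ = 54%, every one a false alarm.

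**6. Number of prior lines.** The Discussion names paclitaxel plus RAM as standard second-line treatment. A patient treated that way has two prior lines if RAM was the immediate prior line, and three or more otherwise. The prior-RAM factor therefore already carries much of this information.

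**The case against.** The strongest reply is that nothing here is an error. Adjusting the analysis for the allocation factors, one of which is PS, is standard, and the sample size reproduces without more covariates. Supportive adjusted models are commonly left to the statistical analysis plan, which is not shown, and the article says all analyses will be fixed before database lock. All of this stands. What remains is that the article positively names the covariate set for its HR and positively plans the baseline tests; both are stated choices and both can be improved.

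Four stronger readings are tempting and are not supported:

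- *Power is being lost.* A reader might infer this, but it is conditional. No section says how prognostic the lesion sum is in this population, and the gain is about 0 if it is not prognostic.
- *Extending the Cox model raises the power of the primary analysis.* It does not while the decision rests on the log-rank test.
- *A non-significant imbalance could push the result across the decision line.* Take 23/55 against 32/55 (chi-squared p = 0.086). At log-HR 0.4 the shift is exp(0.4 × 9/55) = 1.07, moving 0.70 to 0.75, short of the critical HR exp(−1.2816 × 2/√103) = 0.777. Crossing it needs a stronger factor, such as one with HR 2: exp(0.693 × 9/55) = 1.12, giving 0.78. Chance imbalance falls either way and is already covered by the 0.10 error rate.
- *The baseline tests will choose the covariates.* The article attaches no decision to them.

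**Conclusion.** The point holds as an available improvement, not as a flaw in the validity of the design. The plan leaves unused a baseline value that its own entry and imaging rules make obtainable for every eligible patient. Its other stated use of baseline data, significance testing between arms, is uninformative after randomisation.

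The size rests on an assumed prognostic strength: about 0 points if the covariate is not prognostic, and about 2 to 6 points over the allocation-factor Cox model for a log-HR of 0.2 to 0.4 per SD. Stronger covariates would bring more, but nothing in the article supports assuming them. Type I error is essentially the same in both models. The power gain is realised only if the one-sided 0.10 test is taken from the extended model; otherwise the benefit is a more precise HR. The conclusion on baseline tests needs no prognostic assumption, but it affects reporting only.

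**What to change.** 1. Before any by-arm outcome is seen, pre-specify a Cox model for PFS and OS with treatment, the three allocation factors and the log baseline sum of target-lesion diameters. Number of prior lines is optional because it overlaps the prior-RAM factor. Treatment and the allocation factors already use 5 degrees of freedom against about 103 events, so the list should stay short. In an open-label trial, fixing it only before database lock is later than it needs to be.
2. State the model's role. To gain power, take the one-sided 0.10 PFS test from it, which replaces the stratified log-rank test as primary and needs a documented amendment. If the log-rank test stays primary, name the model as a supportive analysis that sharpens the HR only.
3. Replace the between-arm tests of patient characteristics with counts, means and medians by arm.

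The cost is a short change of text, with no extra patients, visits or scans. The article reports recruitment as ongoing since January 2023, so the timing of the change should be recorded. One small downside: the adjusted HR is conditional and lies slightly further from 1 than the planning value of 0.70 (0.69 to 0.67 in the simulation at log-HR 0.2 to 0.4). The report should say so when comparing the two.
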